### Blinding

Blinding patients and/or therapists for treatment allocation is not possible. One trained researcher who is blinded for therapy modality will perform all measurements.

### Intervention

Participants in the EXP group receive a 4-week training period with the ReHab-TOAT approach at a frequency of 3 sessions of 1.5 h per week. During a previous feasibility and pilot study, a 4-week training period with ReHab-TOAT seemed to be a feasible intervention period in which clinically relevant results could be achieved. An overview of a training session of ReHab-TOAT can be found in Table 1. One session of ReHab-TOAT can be divided into five phases, where the results of the assessment define the subsequent phases, especially the content, and start settings used for the part of training with the remote handling device. Based on patient’s individual needs, the therapist may adapt this training content and parameters like feedback, intensity and extent continuously during the session [46–48].

**Table 1 Tab1:** ReHab-TOAT session

Phase	Elements	Aim of the phase	Approximate timing within the sessions
Assessment	• Patient performs 4 activities of daily living under real-life conditions • Skill analysis by PT or OT • Patient rates performance using VAS	• Skill analysis • Choice of activities that will be practised for 1 week (done at the start of each week)	10 min
Preparation	• Preparative exercises for arm and shoulder joints and muscles	• Making the arm and shoulder flexible/supple	10 min
Training with haptic feedback	• Patient performs sets of exercises • Task segmentation is used (first isolated components are trained, later combinations (chaining)) • Dexter^TM^ is used to generate haptic feedback	• Improving (the components of) the activities chosen	50 min with resting periods in-between
Re-assessment	• Patient performs the 4 activities of daily living under real-life conditions • Patient rates performance using VAS • Tips on performing the activities in the home environment	• Skill analysis • Motivation patient • Encourage practice in real-life circumstances	10 min
Homework	• Strength and mobility exercises • Continuing using their affected arm in discussed daily activities	• Encourage practice in real-life circumstances	Based on individual needs

*PT* physical therapist, *OT* occupational therapist, *VAS* visual analogue scale

The main goal of ReHab-TOAT is for the patient to obtain an independent use of the affected arm during the training sessions but especially in other activities and situations, like the home situation of the patient. Therefore, one aspect in all phases of ReHab-TOAT is to facilitate the generalization of training effects towards other/different activities and contexts. Generalization is obtained through various strategies, for example by creating different contexts during practice, giving advice during training and also for non-trained activities and situations, emphasizing achievements during training to raise self-confidence in using the affected arm-hand, discussing and evaluating homework assignments with the patient and caregivers to stimulate training and using the affected arm without supervision and in different contexts [49–54].

During the training phase with haptic feedback, a remote handling device with bespoke software is used (Fig. 2). This device is called Dexter™ (developed by Veolia Nuclear Solutions UK, Didcot, UK). It is an advanced remote manipulator system which is used in a master-slave construction to replicate the flexible, fine motor function of humans in an environment where humans cannot go, like nuclear waste disposal sites. It can be used to manipulate proprioception by giving haptic feedback to the arm of the participant in six degrees of freedom, resulting in a high range of motion for the user (see the Appendix for more information). A software-driven interface was designed by the Expertise centre for Digital Media (EDM) of Hasselt University (Belgium) in collaboration with Adelante, to facilitate therapists to work with their patients without the need of a technician to be present. However, in this project, for practical and safety reasons, a technician will always be present during the ReHab-TOAT sessions.

**Fig. 2 Fig2:**
[figure not shown]
Relationship between Dexter^TM^ and exercises/games on screen and therapist interface

The whole intervention is patient-centred and patient-tailored. Furthermore, the therapy is constantly monitored by the therapist and adaptations to the training can be made instantaneous. If changes in one or more of the following factors occur at any moment during the training session, possible adaptations to the training will be discussed with the patient: changes in pain level, changes in movement speed, changes in compensation strategies, changes in strength, changes in movement flexibility and selectivity, changes in range of motion of the arm, changes in muscle fatigue or general fatigue, changes in concentration possibilities, changes in motivation of the patient, changes in perceived fun, changes in the (motor) performance of the tasks and changes in the performance of the exercise (e.g. less repetitions). If both therapist and patient together decide which adaptations are necessary, these adaptations can be made instantaneous on an ‘as needed’ basis, both in terms of training intensity and (skill) training content.

Each training session will be recorded by the therapist in a training log. Information about the training, for example about the sort of preparation exercises used, the intensity of the exercises, session duration and resting periods, feedback given by the robotic device, evaluation of the present training session, evaluation of the time between the training sessions, perceived differences in their home situation, issues in participant-therapist interaction, etc., will be reported. This information will be evaluated at the end of the study. Both therapists involved in the delivery of the training regularly meet to discuss the treatment and progress of patients.

In case of any missed intervention or measurement sessions, the research coordinator will re-schedule this session as soon as possible. Finally, in case a participant wants to stop the intervention, (s)he can stop at any moment without providing the reason behind his/her decision.

### Outcome measures

An overview of all outcome measures and measurement time points can be found in Table 2. The primary outcome of this RCT will be the *motor performance* of the affected arm-hand, measured using the upper extremity section of the Fugl-Meyer Assessment (FMA). The 33 items assess reflexes, movements and coordination of the shoulder, elbow, wrist and hand. The FMA has been found to be reliable and valid in stroke patients [55–57] at the impairment level [56, 58, 59]. The FMA has been used as a gold standard against which other scales have been validated [59].

**Table 2 Tab2:** Overview measurements and time points

		Study period										
**Timepoints**		**Enrolment**	**Allocation**	**Post-allocation**								
				***Baseline***				***Intervention***	***Follow-up***			
		*T* _*-1*_	*T* _*0*_	*T* _*BL1*_	*T* _*BL2*_	*T* _*BL3*_	*T* _*BL4*_		*T* _*FU*_	*T* _*FU3m*_	*T* _*FU6m*_	*T* _*FU9m*_
**Enrolment**												
Eligibility screening		X										
Informed consent		X										
Allocation			X									
**Interventions**												
ReHab-TOAT (EXP)								X				
Therapy-as-usual (CONTR)								X				
**Assessments**												
Function level	*UAT*		X									
	*MAS*		X									
	*FMA*			X	X	X	X		X	X	X	X
Activity level	*ARAT*			X	X	X	X		X	X	X	X
	*MAL*			X	X	X	X		X	X	X	X
	*Accelerometry (each for 5 consecutive days)*			X					X	X	X	X
Personal factors	*Patient demographics and characteristics*		X									
	*EuroQol-5D*			X					X	X	X	X
External factors	*Single question on any occurred events that may influence measurements*			X	X	X	X		X	X	X	X
	*CarerQol (re. caregiver)*			X					X	X	X	X
	*Single question on amount and content of support (re. caregiver)*			X					X	X	X	X
***Evaluation***												
System Usability Scale									X			
Questionnaire on user experience of technology used				X					X			

*T..* time of measurement, *BL* baseline, *FU* follow-up, *m* month, *Interv* intervention, *EXP* experimental, *CONTR* control, *UAT* Utrechtse Arm Test, *MAS* modified Ashworth Scale, *FMA* Fugl-Meyer Assessment, *ARAT* Action Research Arm Test, *MAL* Motor Activity Log, *SUS* System Usability Scale

Secondary outcome measures will gauge the ICF level of activity and quality of life of the patient and his/her caregiver and will evaluate the usability of the intervention, including both the approach developed and the technology used. Arm-hand *capacity* will be measured using the Action Research Arm Test (ARAT), including grasp movements and reaching movements. The ARAT has been proven to be a reliable, valid and sensitive instrument for upper limb function measurement, which does not show a ceiling effect [60–64]. *Perceived* arm-hand skill performance will be measured using the Motor Activity Log (MAL). The MAL is a semi-structured interview to assess the frequency, quality of use and quality of use of the affected limb during the performance of daily living activities. The MAL has been shown to be a reliable and valid tool for the measurement of arm-hand activity in stroke patients [65]. To measure *actual* arm-hand skill performance, also in different contexts, 3D accelerometers (AX3, Axivity Ltd, UK) are used. Signals from these sensors will be analysed to gauge the actual amount of arm-hand use during daytime, according to the protocols described by Lemmens et al. [66] and Franck et al. [38]. The EuroQol-5D (EQ-5D) will be used to measure the quality of life of the patient regarding perceived health status [67]. The EuroQol-5D has good psychometric properties [68]. To measure the quality of life of the patients’ caregiver, the Care-related Quality of Life instrument (CarerQoL) will be used. It combines a subjective burden measure of the caregiver’s situation with a valuation of personal well-being on a VAS. The CarerQoL has been proven to be feasible, valid and reliable in measuring the impact of caregiving [69–71]. In addition to the CarerQoL, one single question will be asked to measure the amount and content of support the caregiver provides. For evaluation of the used technology and the developed training approach of ReHab-TOAT, the System Usability Scale (SUS) and a self-developed questionnaire will be used. The SUS has been widely used in the evaluation of many systems and is a reliable and valid measure of perceived usability [72–76]. The questionnaire on the user experience of technology used was developed by researchers, technicians and clinicians from Adelante rehabilitation centre and Hasselt University. The questionnaire is based on the Technology Acceptance Model (TAM) and the Unified Theory of Acceptance and Use of Technology (UTAUT) [77] and is established to evaluate the technology-assisted training concept developed. The questionnaire evaluates the perceived benefits, struggles and necessary improvements related to ReHab-TOAT.

Furthermore, a single question gauging the occurrence of any event over the last 2 weeks that may influence the results of the treatment or the measurements (e.g. the patient having had the flu in the past 2 weeks) will be posed. Patients’ demographics and characteristics will be recorded at entry into the study, as will the presence of any restricting form of spasm (Modified Ashworth Scale (MAS)) and AHF status (UAT) [37]. Also, the amount and content of any therapy the participant may potentially receive as care as usual during his/her participation in the project will be recorded in a questionnaire during each measurement session.

### Data collection and management

Data collection of all participants is done by one independent, trained and blinded physical therapist of Adelante rehabilitation centre to eliminate any potential inter-observer differences. All data and results will be handled confidentially. All data will be coded during measurement. Coding will be done using a combination of numeric and alphanumeric characters, which are not related to the participant. Non-coded data (e.g. participant’s name) will be stored separately by the study supervisor. All data from the RCT will be stored in a GDPR-compliant data management system (CASTOR repository (https://www.castoredc.com/; CASTOR, Amsterdam, The Netherlands)). Data entry in Castor is verified by the coordinating researcher, who will also create a locked data file at the end of the study. The coordinating researcher, the study supervisor and the assessing physical therapist have reading access to the data management system. Only the coordinating researcher has full access to the data and the data management system with all rights.

Different retention strategies are used to ensure full data collection and to minimize any withdrawal of participants. The researchers stay in contact with the participants between the training and/or measurement appointments to ask if everything is okay and to kindly remind them of their appointments. Furthermore, the researchers support them with organizing transportation to the appointments and refund the transportation costs quickly. During each appointment, the researchers provide catering for the participants and plan enough time for each session so that nobody feels stressed.

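### The single blinded assessor has unrestricted reading access to a database that would hold arm-revealing usability data, so blinding of the FMA and ARAT ratings is not protected

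*Protocol article*

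**What the plan says.** The Blinding section concedes that "Blinding patients and/or therapists for treatment allocation is not possible" and then places the whole burden on one person: "One trained researcher who is blinded for therapy modality will perform all measurements". The Data collection and management section repeats this: "Data collection of all participants is done by one independent, trained and blinded physical therapist of Adelante rehabilitation centre".

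That section goes on to say "All data from the RCT will be stored in a GDPR-compliant data management system" (Castor), and then: "The coordinating researcher, the study supervisor and the assessing physical therapist have reading access to the data management system". No limit to the assessor's own forms, to arm-neutral fields or to the time after lock is given. The next sentence reserves complete rights over the data and the system to the coordinating researcher.

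Table 2 schedules the "System Usability Scale" at the visit directly after the intervention (T_FU), and the technology questionnaire at T_BL1 and T_FU. The Outcome measures section says these instruments evaluate the ReHab-TOAT approach and its technology. It also describes a therapy questionnaire, which covers "the amount and content of any therapy the participant may potentially receive as care as usual during his/her participation in the project" and "will be recorded in a questionnaire during each measurement session".

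**The concern.** The primary outcome, the upper-extremity FMA, and the ARAT depend on an observer's judgement, and the same observer scores all participants at all visits. No second rater is described who could reveal drift. If that observer learns the arm, any expectation about the new device enters the between-arm difference directly. The Discussion intends to attribute changes in the experimental arm relative to control to the intervention, and that attribution needs ratings made without knowledge of the arm.

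The difficulty lies in what the article states. It declares the assessor blinded and, a few sections later, gives the assessor reading access to a system said to hold all trial data.

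**Working it through.** This is mainly a matter of setting passages side by side.

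**1. How much rests on the assessor.** With patients and therapists unblinded, the trial is single-blinded through the assessor alone.

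**2. What the assessor could see or hear.**

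| Item | When | Would it reveal the arm? | Basis for the assessor's exposure |
|---|---|---|---|
| System Usability Scale | T_FU | Yes; only EXP participants have used the system | Database: follows from the stated access to a system holding all data. Collection: literal reading only |
| Technology questionnaire | T_BL1, T_FU | Yes once training has taken place; at T_BL1 only if given to one arm, which is not stated | As above |
| Therapy questionnaire | Every session | Only if the participant mentions the study training; it asks about care as usual | Literal reading only for collection; a minor route |
| Earlier FMA scores | All earlier visits | No, but they allow anchoring | Database: as above |
| Allocation record | At randomization | Yes | Not established; the research coordinator records it and Castor is not named |
| Training log | Each training session | Yes | Not established; the therapist keeps it and no storage place is named |

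The coding described in the article hides identity, not arm, and the assessor meets the participant in person.

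**3. Which ratings are exposed.** Table 2 schedules FMA and ARAT at four baseline and four follow-up visits. A usability form completed at T_FU could inform the 3, 6 and 9 month ratings, which are three of the four follow-up ratings. It could inform the T_FU rating only if it came before the FMA that day, and no order is stated.

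**4. The plan's own figure.** The Sample size section gives log-FMA means 1.47 (SD 0.12) and 1.65 (SD 0.11), two-sided alpha 0.01, power 0.90 and 10% loss.
- Pooled SD = √((0.12² + 0.11²)/2) = 0.115; difference = 1.65 − 1.47 = 0.18.
- n per group = 2 × (2.576 + 1.282)² × 0.115² / 0.18² ≈ 12.2, so 13; 13/0.90 = 14.4, so 15. The stated 15 per group is reproduced, and this point does not alter it.
- Assuming log base 10, the planning means are 10^1.47 = 29.5 and 10^1.65 = 44.7 points, a gain of about 15 points.

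**5. Illustration of sensitivity, with assumed biases.** The documents give no estimate of rating bias. Suppose there is no true effect, 13 completers per group, SD 0.115, the alpha of 0.05 from the Statistical analysis section, and a simple two-group comparison in place of the planned mixed model. Then SE = 0.115 × √(2/13) = 0.045, and the rejection probability is Φ(b/SE − 1.96) + Φ(−b/SE − 1.96) for a pro-EXP bias b.

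| Assumed b (log10 units) | As a ratio | Type I error |
|---|---|---|
| 0 | 1.00 | 5% |
| 0.02 | 1.05 | about 7% |
| 0.04 | 1.10 | about 14% |
| 0.06 | 1.15 | about 26% |

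This shows what a given bias would do. It is no evidence that any bias exists.

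**The case against.** The strongest reply is that an article condenses a fuller protocol and data-management plan, where role-based rights and form order normally sit. The sentence reserving complete rights to the coordinating researcher could also mean that the assessor sees less than everything. This has some weight, but the article does more than stay silent: it grants reading access to a system holding all trial data. The sentence on complete rights most naturally separates reading from editing and administration. If a restriction exists, the published text should say so.

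Other parts of the reply stand:

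- **Who collects the usability forms is inferred.** Table 2 lists them under Evaluation, apart from the Assessments block that contains FMA and ARAT. The stated purpose of using one assessor, avoiding inter-observer differences, fits observer-rated tests better than questionnaires.
- **The therapy questionnaire does not in itself disclose the arm.** A reader might infer that it does from its being taken at every session, but its wording confines it to care as usual, which either arm may receive.
- **A reader might infer that allocation or training logs are open to the assessor.** Nothing places either in Castor.
- **Seeing earlier scores is not unblinding.** It applies to both arms and does not by itself favour EXP. Its harm is to the independence of repeated ratings, including the weekly baselines meant to show stability.
- **A reader might infer that a drift of 2 to 3 points would match the whole effect**, since 10% of 29.5 is about 3 points. The Discussion's figure is an improvement exceeding 10% in a different study, not this trial's target. Against the planning gain of about 15 points, 3 points is about one fifth, and no document supports a drift of that size.

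**Conclusion.** The point holds in limited form. The article relies on one blinded assessor and, without stated restriction, gives that person reading access to data that would identify experimental participants through the usability instruments. The literal wording also has the assessor collect those instruments, but this second route is an inference.

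A reader might conclude that blinding is undone and the FMA results are biased toward the device. The documents do not support that: they show missing protection, not actual unmasking, and the size of any bias cannot be estimated. The conclusion assumes that the statement about all trial data covers the usability forms and that no unpublished restriction exists. It is still worth correcting, because this is the only blinding behind an observer-rated primary outcome and the correction costs almost nothing.

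**What to change.** - Until database lock, limit the assessor's Castor rights to the entry forms of the current visit, with no view of usability data, therapy data, any allocation data or earlier scores.
- Have the usability and therapy questionnaires self-completed, or taken by already unblinded staff after FMA and ARAT have been scored.
- Amend the Blinding and the Data collection and management sections to match: state which measurements the blinded assessor performs, who handles the questionnaires, and what the assessor can read.
- Record the assessor's guess of arm at the remaining follow-up visits.
- For ratings already made, check the database access log and report who administered the questionnaires.

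The cost is a small change of user rights and form order. The limit is timing: the Trial status section reports recruitment complete in October 2022 and last assessments expected in November 2023. The change protects only ratings still to come; for past ones, the access log and a plain report are all that can be offered.

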### Sample size

This sample size calculation [78] is based on data gathered in an earlier, small-sized pilot study, featuring pre- and post-intervention measurements, gauging the *order of magnitude* of any potential effect of the ReHab-TOAT treatment in a similar patient group, performed at the Adelante rehabilitation centre. Given the small sample and the skewed distribution, we used a log transformation on those data to estimate the group sizes needed for the RCT.

Given a log-transform of the skewed FMA data gathered during the aforementioned pilot study, a two-sided test and a:Mean (log-transformed) pre-intervention FMA value = 1.47 (sd = 0.12)Mean post-intervention FMA value = 1.65 (sd = 0.11)Power = 0.90Alpha = 0.01Loss-to-follow-up = 10%

fifteen patient-participants in each group, i.e. 30 participants in total, are needed.

Regarding the patients’ caregivers, 30 persons (associated with the aforementioned patients that are eligible and willing to participate) will also be asked to participate.

### Statistical analysis

#### Primary study parameter(s)

Data from the primary outcome measure (FMA) will be tested for normal distribution using a Kolmogorov–Smirnov test. If normally distributed, data will be statistically analysed using a linear mixed model analysis (factors: GROUP and TIME). If, on the other hand, data are found to be skewed, a log transformation will be performed, after which a linear mixed model will be used to analyse the log-transformed data. Generally, alpha will be set at 0.05. In case of multiple comparison of the data post hoc, a Bonferroni approach will be used to avoid spurious potential false positive findings.

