### Eligibility criteria

Adult stroke patients who are currently in the chronic phase after stroke (i.e. post-stroke time longer than 12 months), who suffer from a hemiplegic arm motor impairment with an UAT score between 1 and 3 [37] and who are able to understand and execute a 3-stage verbal command are included in this study. Participants are excluded if they suffer severe non-stroke-related co-morbidity that may interfere with arm-hand function or interfering spasticity in the affected upper limb, i.e. a Modified Ashworth Scale (MAS) score >= 1+ [45].

Patients’ caregivers are included if they are over 18 years of age and provide informal care to the above-mentioned participants. Patient participants will not be excluded if their caregiver does not want to participate in this study. He/she can ask a different caregiver or decide to participate without any caregiver taking part in the study.

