#### Secondary study parameter(s)

The data from the ARAT, the MAL the EuroQol-5D and the CarerQol will be statistically analysed similarly to the data of the FMA. The data regarding patients’ amount of arm-hand use during daytime, derived from the accelerometer signals (according to the protocols described by Lemmens et al. [66] and Franck et al. [38]), will also be statistically analysed similarly to the procedure used to analyse differences in the data of the FMA. Results from the SUS and the questionnaire on user experience of technology used will be reported descriptively. The single questions gauging for any event that may have influenced the patient’s or caregiver’s answer or measurement will only be used to identify/interpret any unexpected measurement and will be reported descriptively. The frequency and content of any additional therapy the participants received during the intervention period will be also reported.

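### A Kolmogorov–Smirnov test on the outcome data, not the residuals, decides whether FMA is analysed in points or on the log scale, so the primary effect measure is not fixed in advance

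*Protocol article*

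**What the plan says.** In the protocol article, under Primary study parameter(s), the FMA data "will be tested for normal distribution using a Kolmogorov–Smirnov test". If the data pass, a linear mixed model with group and time as factors is fitted to them as they stand. If not: "If, on the other hand, data are found to be skewed, a log transformation will be performed", and the same model is fitted to the logs. The section does not mention model residuals. It does not say whether the test is run per visit, per arm or on pooled values, or which form of the KS test is meant.

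Under Secondary study parameter(s) the rule is extended: "The data from the ARAT, the MAL the EuroQol-5D and the CarerQol will be statistically analysed similarly to the data of the FMA". Arm use from accelerometry "will also be statistically analysed similarly to the procedure used to analyse differences in the data of the FMA". No offset, alternative transformation or rule for zero values is given.

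The Sample size section reports that the pilot FMA data were skewed and sizes the trial on the log scale only: mean 1.47 (SD 0.12) before and 1.65 (SD 0.11) after the intervention, two-sided alpha 0.01, power 0.90 and 10% loss, giving 15 per group.

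**The concern.** A linear mixed model assumes roughly normal residuals and random effects. It does not assume normal outcome values. Outcome values also carry visit effects, any treatment effect and, if pooled, the correlation between eight measurements on each patient, whereas the KS test assumes independent values. The test is therefore aimed at the wrong object.

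The two branches also answer different questions. The raw branch estimates a difference in FMA points. The log branch estimates a ratio. Which one becomes the primary result depends on the trial's own data, and the result may not be on the scale used to justify the sample size.

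The same gate then governs five further outcomes, and a logarithm does not exist for a score of zero.

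**Working it through.** **1. The plan's own figure.** Inputs from the Sample size section: difference 1.65 − 1.47 = 0.18; pooled SD = √((0.12² + 0.11²)/2) = 0.1151. With n = 2(z₀.₉₉₅ + z₀.₉₀)²·SD²/difference²:

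2 × (2.576 + 1.282)² × 0.01325 / 0.0324 = 12.2, so 13 per group; 13/0.90 = 14.4, so 15.

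The stated 15 per group is reproduced, on the log scale. Base 10 is inferred, because 10^1.47 = 29.5 and 10^1.65 = 44.7, whereas natural logs would give 4.3 and 5.2. In the two candidate effect measures the pilot change is a ratio of 10^0.18 = 1.51, or 44.7 − 29.5 = 15.2 points between geometric means.

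**2. How often the gate picks each scale.** Simulated KS test at 5% with estimated mean and SD, in the plain form and with the Lilliefors correction. The correlations are assumptions. The log SD of 0.115 comes from the pilot figures.

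| True data | Values tested | Log scale chosen, Lilliefors | Log scale chosen, plain KS |
|---|---|---|---|
| Exactly normal, correlation 0.8 | 30 patients × 8 visits | about 29% | about 4% |
| Exactly normal, correlation 0.9 | 30 patients × 8 visits | about 46% | about 9% |
| Log-normal, log SD 0.115 | 30 patients, one visit | 18% | 0.3% |

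Repeat runs gave 27 to 49% (Lilliefors) and 3 to 11% (plain) for the pooled rows. In those rows the raw-scale model is correct, yet the gate often leaves it. In the last row the log scale is correct, and the gate usually misses it.

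**3. The gate reacts to the treatment effect.** With log-normal data pooled over eight visits at correlation 0.9, the log scale is chosen in 46% (plain) or 79% (Lilliefors) of trials with no effect, and in 77% or 97% with the pilot effect of 0.18.

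**4. What this does to inference.** The two-stage rule was simulated with 15 per arm, eight visits, the pilot means and SDs, pooled Lilliefors, an assumed correlation of 0.85, and a contrast of mean follow-up against mean baseline standing in for the mixed model.

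- No effect: the rule rejects in 5.1% (log-normal data) and 5.3% (normal data) of trials, against a nominal 5%.
- Pilot effect 0.18: power is about 100% on either scale.
- Small effect 0.03: raw and log analyses disagree on significance in about 7 to 9% of trials, and up to about 12% in repeat runs. On normal data one run gave two-stage power of 66%, against 72% if raw scores were always used.

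**5. Zeros.** log(0) is minus infinity. With an added constant c, a change from 0 to 2 equals log₁₀((2 + c)/c), which is 2.30, 1.32, 0.70 or 0.48 for c = 0.01, 0.1, 0.5 or 1. A change from 20 to 22 stays near 0.04 throughout. If zeros occur, an unstated constant would drive the result.

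**The case against.** The strongest reply is that no damage to the primary test has been shown. This stands: type I error is essentially preserved, and at the effect the trial was sized for the scale makes no difference to significance. A reader might infer that the pre-test invalidates the primary p-value; the check in step 4 does not support that. Nor is the test wholly uninformative, since marginal skew is imperfect but relevant evidence about skew in residuals and random effects.

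The rates also depend on choices the protocol does not state. The pooled and single-visit rows are alternative readings, not one estimate, and plain KS gives much lower rates than Lilliefors. This also stands, but it is part of the difficulty: the same data could reach different scales under different readings of one sentence.

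Two stronger readings are tempting. One is that the log would make matters worse because bounded scales are left-skewed. A log does worsen left skew, but the only evidence on the FMA distribution is a pilot in which a log was thought suitable, so this is hypothetical for the primary outcome. The other is that severely affected patients will be lost because their scores are zero. The protocol does enrol patients "who suffer from a hemiplegic arm motor impairment with an UAT score between 1 and 3", so low scores are plausible, but it gives no scale minima and does not say that such patients would be dropped. A statistical analysis plan may add an offset or another transformation.

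**Conclusion.** The point holds in a limited form. This is not missing detail. It is a stated decision rule that leaves the primary effect measure open until the data are seen, rests on the wrong object, and can move the analysis off the scale used for sizing. Its unreliability runs in both directions: about 29 to 46% (Lilliefors) or 4 to 9% (plain KS) wrongly sent to the log scale under pooling, and only 18% or 0.3% rightly sent there at a single visit. These figures rest on assumed correlations of 0.8 to 0.9, base-10 logs and the pilot SD.

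The consequence is ambiguity about what is estimated and, if the true effect is small, some dependence of significance on the scale. Type I error and the sample size are not in question. The zero-score problem is conditional on a secondary scale reaching zero and does not touch the FMA. The point should be corrected before analysis, but it does not threaten the trial's validity.

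**What to change.** Remove the KS gate. Name one FMA scale for the primary analysis now and report the other as a sensitivity analysis. The log scale matches the Sample size section and leaves N at 15 per group. If points are preferred for interpretation, restate the effect and SD in that section in points and check N again. Use residual plots from the fitted model as diagnostics only, not to choose the primary scale.

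For ARAT, MAL, EuroQol-5D, CarerQol and accelerometry, name in advance an analysis that admits zero scores, such as the untransformed mixed model.

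The cost is a few sentences of plan wording and a little programming for the sensitivity analysis. Recruitment, visits and data collection are unaffected. The change should be dated and made before the data are analysed.
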